## Abstract

**Background:**

Diabetic distal symmetric polyneuropathy (DSPN) is one of the most common microvascular complications of diabetes mellitus, and it has become a major public health problem worldwide because of its high and increasing prevalence, morbidity, and disability rate. The current medications for DSPN are not entirely satisfactory. Preliminary studies indicated that the Chinese herbal TangBi Formula may alleviate signs and symptoms and improve the velocity of nerve conduction in patients with DSPN. This study was designed to determine if Chinese herbal medicine used in combination with conventional treatment is more effective than conventional treatment alone.

**Methods/design:**

We are conducting a multicenter, placebo-controlled, double-blind, randomized, controlled clinical trial as a means of assessing the therapeutic effects of traditional Chinese medicine (TCM) treatment. A total of 188 patients will be randomized in a 1:1 ratio to a treatment group (TangBi Formula plus mecobalamin) and a control group (placebo plus mecobalamin). The test period lasts 6 months, during which all of the patients will be given standard medical care as recommended by established guidelines. The primary outcome will be development of differences in changes in clinical symptoms and signs in patients and changes in Michigan Diabetic Neuropathy Score (MDNS) between the two groups before and after treatment. The secondary outcome will be changes in nerve conduction velocity and in single clinical signs and symptoms. Safety assessments and adverse events will also be evaluated.

**Discussion:**

We postulate that patients with DSPN will benefit from therapy that includes TCM. If successful, this work will provide an evidence-based complementary therapeutic approach for treatment of DSPN.

**Trial registration:**

ClinicalTrials.gov, NCT03010241. Registered on 2 January 2017

**Electronic supplementary material:**

The online version of this article (doi:10.1186/s13063-017-2345-1) contains supplementary material, which is available to authorized users.

## Background

The latest figures from the International Diabetes Federation indicate that as of 2015, more than 415 million people worldwide have diabetes, and this number is expected to increase to 642 million by 2040. China has the largest number of people with diabetes (109.6 million) [1]. An epidemiological survey done in China shows that, among adults in China, the estimated overall prevalence of diabetes is 10.9% [2]. Diabetic individuals have higher rates of premature death, functional disability, and coexisting illnesses than their healthy counterparts. During its clinical course, diabetes may be accompanied by several other microvascular and macrovascular complications [3]. Some of the most serious and deleterious complications of diabetes, such as foot ulcers, are associated with diabetic neuropathy. Distal symmetric polyneuropathy (DSPN) is the most common neuropathic complication of diabetes. Up to 50% of patients with neuropathy experience symptoms, including burning pain, stabbing sensations, paresthesia, hyperesthesia, and deep aching pain, which typically becomes worse at night [4–6]. The end-stage complications of neuropathy, such as foot ulceration and amputation, are associated with a dramatic increase in health care costs and a decrease in quality of life [7–9]. Painful neuropathic symptoms can interfere with sleep, decrease quality of life, and increase psychosocial distress [10]. Currently, the treatment for DSPN chiefly includes diabetic management via tight glucose control and pain relief for neuropathy [11, 12]. Medications such as narcotic analgesics, tricyclic antidepressants, anticonvulsants, phenothiazines, nonsteroidal anti-inflammatory drugs, and opioids have all been used with limited success. Adverse effects such as drowsiness, lethargy, and unsteadiness are frequent [13].

In their search for more effective treatment strategies for DSPN and ways of slowing the overall progression of the disease, many patients in China seek help using traditional Chinese medicine (TCM). Chinese herbal medicine (CHM) is one part of TCM and has a long history of use in China. CHM treatments for diabetes, including DSPN, include both oral and topical medications, used alone or in combination with Western conventional medicine. Several randomized clinical trials have suggested that CHM can alleviate symptoms, improve motor conduction velocity (MCV) and sensory conduction velocity (SCV), and delay the progression of DSPN [14–17].

A meta-analysis of 18 randomized clinical trials including 1575 cases of DSPN demonstrated a beneficial effect of TCM on clinical symptoms. In that analysis, treatment groups showed significant differences from control groups, without any serious side effects (*P* < 0.01) [18]. However, a subsequent meta-analysis of ten randomized controlled studies established that there is insufficient evidence regarding the efficacy of CHM for the treatment of DSPN because of the pronounced clinical heterogeneity of the included studies and small sample sizes of the included trials [19].

TangBi Formula consists of five herbal granules, namely *Astragalus membranaceus* (Huangqi), cassia twig (Guizhi), *Ligusticum chuanxiong Hort* (Chuanxiong), *Radix Paeoniae Alba* (Baishao), and *Caulis Spatholobi* (Jixueteng), that have been used to treat DSPN at the Outpatient Department of Guang An Men Hospital of the China Academy of Traditional Chinese Medicine for nearly three decades. Relevant case reports have demonstrated that TangBi Formula alleviates the signs and symptoms of diabetic peripheral neuropathy (DPN) and improves NCV measured by electromyogram (EMG) [20].

For all of these reasons, the efficacy of TangBi Formula in patients with DSPN is worth investigating because of the pleiotropic effect. In the present study, we assumed that TangBi Formula in addition to conventional treatment may be more efficacious than conventional treatment with respect to the alleviation of the signs and symptoms of DSPN and improvement in NCV as indicated by EMGs. If successful, the study may provide an evidence-based complementary therapeutic approach to slow or prevent the clinical progression of DSPN in patients. In this protocol, we detail the overall study design and approach. This project was supported by the Special Scientific Research Fund of Traditional Chinese Medicine Profession of China (grant number 201507001-11), and it was registered with ClinicalTrials.gov (NCT03010241; registered on 2 January 2017).

## Methods/design

### Study objectives

This clinical trial is designed as a multicenter, randomized, double-blind, placebo-controlled, parallel-group project. The trial flow is illustrated in Fig. 1. A superiority trial is planned to test the hypothesis that TangBi Formula used in combination with conventional treatment is more effective than conventional treatment alone in alleviating the clinical symptoms of DSPN and improving NCV of patients with DSPN. The treatment duration is set for 6 months.

**Fig. 1 Fig1:**
[figure not shown]
Entire design of this trial. *DSPN* Distal symmetric polyneuropathy

### Design overview

The study design will integrate rigorous contemporary clinical research methodology in accordance with the principles set out in the Declaration of Helsinki and good clinical practice (GCP) guidelines according to the theory that guides the appropriate use of TCM in clinical practice. The rigorous design, organization, and conduct of the trial are supervised by a steering committee comprising two members from each participating center in addition to the chairman, scientific coordinator, and statistician. Six clinical centers in mainland China will participate in the trial, including Guang’anmen Hospital of the China Academy of Chinese Medical Sciences, the First Affiliated Hospital of Liaoning University of Traditional Chinese Medicine, the First Affiliated Hospital of Anhui University of Traditional Chinese Medicine, Hubei Hospital of Traditional Chinese Medicine, Zhengzhou City Hospital of Traditional Chinese Medicine, and Hebei Yiling Hospital. Data management and statistical analyses will be performed by independent data handlers and data analysts at the Institute of Basic Research in Clinical Medicine, China Academy of Chinese Medical Sciences. All of the patients must personally sign and date an informed consent document before randomization.

### Inclusion criteria

The inclusion criteria are outlined below.Meet the diagnostic criteria of diabetic DSPN:Have a history of type 2 diabetes.– Diagnosis of type 2 diabetes mellitus [21] is defined as fasting plasma glucose ≥ 126 mg/dl (7.0 mmol/L)
Fasting is defined as no caloric intake for at least 8 h.*
ORTwo-hour plasma glucose ≥ 200 mg/dl (11.1 mmol/L) during an oral glucose tolerance test. The test should be performed as described by the World Health Organization using a glucose load containing the equivalent of 75 g of anhydrous glucose dissolved in water.*
ORHbA1c ≥ 6.5% (48 mmol/mol). The test should be performed in a laboratory using a method that is National Glycohemoglobin Standardization Program-certified and standardized to the Diabetes Control and Complications Trial assay.*
ORIn patients with classic symptoms of hyperglycemia or hyperglycemic crisis, a random plasma glucose ≥ 200 mg/dl (11.1 mmol/L).*
– Patients with type 2 diabetes and glycemia, effectively managed or not.

(b).The main symptoms are numbness of the limb extremities; spontaneous pain (e.g., burning pain, tingling, dull pain); and paresthesia, usually distributed like gloves or socks, starting from the lower limbs, symmetrically; foot pain sense and diminished temperature sensation, vibration decreased or disappeared, but motor function basically intact.(c).EMG NCV decreases: We plan to diagnose patients with EMG NCV decreases when an EMG indicates that any of the 16 nerves of the bilateral motor nerves (median nerve, ulnar nerve, sural nerve, and superficial peroneal nerve) and the sensory nerves (median nerve, ulnar nerve, peroneal nerve, and tibial nerve) is conducting signals significantly lower than in healthy individuals.

2.The patient’s age is between 30 and 70 years.3.The patient provides signed informed consent.

*In the absence of unequivocal hyperglycemia, results should be confirmed by repeat testing.

### Exclusion criteria

Exclusion criteria include the following:Recent use of antioxidants, such as vitamin E or vitamin C; acute infection; liver or kidney dysfunction; acute complications of diabetes; severe cardiovascular and cerebrovascular disease; and neuropathy caused by long-term alcohol consumption or other factors.Cardiovascular, liver, kidney, hematopoietic system, or other serious primary disease; serum transaminase more than double the normal value; serum creatinine (SCr) greater than the upper limit of normal; and psychiatric patients.Pregnancy, preparation for pregnancy, or lactation, or any history of drug allergy.Participation in another drug clinical trial or use of any other drug within the previous month.Systolic blood pressure > 160 mmHg or diastolic blood pressure > 100 mmHg.Having diabetic ketoacidosis, any other type of ketoacidosis, or severe infection within the previous month.Any excessive consumption of alcohol or any consumption of psychoactive substances, drug abuse, or drug dependence during the past 5 years.Any other disease or condition capable of reducing the possibility of entry or complicating the entry as determined by the researchers’ judgment, such as frequent changes in work environment, unstable living environment, or similar factors that could cause loss of contact.

### Conditions and procedures for withdrawal of study subjects

Subjects who become in eligible to continue participating in the study must be withdrawn.

### Researcher’s decision

The investigator may decide to remove subjects from the study for any of the following reasons:During the study, the subject may experience some complications or physiological changes rendering him or her unsuitable for further participation.During the study, the subject may be poorly compliant, such as failure to take at least 80% and no more than 120% of the prescribed amount of medicine.Any breaking of blindedness or emergency unsealing of patient information.Any use of drugs prohibited by the study plan during the study period.

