### Subjects’ voluntary withdrawal

As stipulated in their informed consent forms, the subjects have the right to withdraw from the study at any time. Participants who do not formally withdraw from the study but cease to accept medication and undergo testing or who become impossible to contact are also considered withdrawn. The researcher should realize and record the reasons for subjects’ withdrawal to the greatest extent possible, noting whether the treatment is obviously ineffective, difficult to tolerate owing to adverse reactions, or whether the patient cannot continue to participate in clinical research for some other reason, such as economic or personal factors. Whatever the reason, the case record should be retained; the last test results will be carried forward to the final result; and a full dataset will be analyzed for the treatment’s efficacy and adverse effects.

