### Sample size

According to the preliminary study of TangBi prescription data, the placebo group scale (MDNS) score difference was 3.45 and the TangBi prescription scale score was 4.14, with an SD of 1.33. The sample size was estimated using a hypothesis test formula of measurement data: *N* = 2 × [(Zα + Zβ) × δ/*d*]^2^, where *N* is the sample size and δ is the estimated SD, *d* is two groups’ continuous variable mean difference, and Zα and Zβ are the corresponding standard normal differences. Supposing α = 0.05 and β = 0.10, according to the one-sided check table, the quantile Zα = 1.64485 and Zβ = 0.84162, and these are entered into the formula. It is estimated that a sample size of 78 subjects per group will be required, taking into account 20% dropout and withdrawal. This results in 188 participants in total. Intention-to-treat analysis will be used to minimize bias due to dropouts.

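### Discretionary removal from the study for poor compliance, a code break or prohibited drugs creates avoidable missing week-24 outcomes and undercuts the promised intention-to-treat analysis

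*Protocol article*

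**What the plan says.** Under Researcher's decision the protocol article says "The investigator may decide to remove subjects from the study for any of the following reasons". Three of the listed reasons matter here:

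- poor compliance, described as "failure to take at least 80% and no more than 120% of the prescribed amount of medicine";
- "Any breaking of blindedness or emergency unsealing of patient information";
- "Any use of drugs prohibited by the study plan during the study period".

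A fourth reason, complications or physiological changes, is also listed; the point does not depend on it. The preceding section adds a mandatory rule: subjects who become ineligible "to continue participating in the study must be withdrawn".

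The next section, Subjects' voluntary withdrawal, says what happens to the outcome: "Whatever the reason, the case record should be retained; the last test results will be carried forward to the final result". Statistical analysis repeats a carry-forward rule for a missing main variable in the FAS. That set comprises randomized subjects who received at least one treatment. The same section defines a PPS that requires 80–120% of the prescribed dose.

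Sample size states: "Intention-to-treat analysis will be used to minimize bias due to dropouts".

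**The concern.** Compliance, use of prohibited drugs and code breaks all arise after randomization. Each can depend on the assigned treatment, for example through tolerability, persisting symptoms or an adverse event that prompts unblinding. An intention-to-treat comparison needs the outcomes of exactly these patients. The removal rule lets the investigator end their follow-up, and the analysis then fills the gap with an earlier value. The patient stays in the denominator, but the week-24 outcome under the assigned treatment policy is never observed.

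The plan would thus generate missing data by its own procedure, in addition to what patients cause by withdrawing consent or losing contact. At stake is the credibility of the FAS result. If the arms differ in how often or how early patients are removed, carry-forward turns that difference into an apparent treatment difference.

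**Working it through.** **Inputs, all from the protocol article**

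- Sample size: mean MDNS change 3.45 on placebo and 4.14 on TangBi; SD 1.33; 20% allowance for dropout and withdrawal; 188 in total.
- Abstract: 1:1 allocation, so 94 per arm.
- Primary outcome measures: MDNS before treatment and at weeks 12 and 24.
- Secondary outcome measures: NCV before treatment and at week 24.

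**The plan's own figures**

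Planned difference: 4.14 − 3.45 = 0.69. With n = 2[(Zα + Zβ) × SD/d]², two-sided 5% and 90% power give 78.08, matching the stated 78 per group. Then 78 × 1.2 = 93.6, rounded to 94 per group and 188 in total. (The quantiles printed in that section give 45.9 instead; that is a separate matter and does not affect this point.) The 20% allowance applied to 188 is 37.6, about 38 patients. The article does not divide it among consent withdrawal, lost contact and investigator removal.

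**What carry-forward does to a removed patient**

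- Removed before week 12: only the baseline MDNS exists, so the carried-forward change is 0.
- Removed between weeks 12 and 24: the week-12 MDNS can be carried.
- NCV has no value between baseline and week 24. If the same rule is applied to it, any removal before week 24 gives a change of 0.

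**Illustration for MDNS (the removal shares are assumptions)**

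Let p_T and p_C be the shares removed before week 12. Suppose these patients would otherwise have had their arm's mean change. The expected FAS difference is

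D = (1 − p_T) × 4.14 − (1 − p_C) × 3.45.

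- Placebo loses 5 percentage points more: D rises by 0.05 × 3.45 = 0.1725, about 0.17, and 0.1725/0.69 = 25%.
- TangBi loses 5 percentage points more: D falls by 0.05 × 4.14 = 0.207, about 0.21, and 0.207/0.69 = 30%.
- If both arms truly change by 3.45, a 5-point imbalance alone produces a spurious difference of about 0.17, with its sign set by which arm loses more.
- Equal removal of 5% in both arms: D = 0.95 × 0.69 = 0.66, a dilution.

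Five percentage points of 94 is 4.7, so the imbalance in question is about five patients in one arm.

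**Is removal needed for any analysis?**

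The compliance range in the removal rule is the same 80–120% that defines the PPS. Non-compliers are therefore already set aside there, and Comparison of factors affecting test evaluation tabulates compliant and non-compliant cases by group. Neither use requires that follow-up end.

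**The case against.** Several points on the other side are fair, and most of them stand as limits on size.

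- **Removal is optional and masked.** The text says the investigator may remove, and Intervention measures masks investigators to assignment. This limits differential removal. It does not help after a code break, when the allocation may be known, and masking does not stop real differences between arms in compliance or prohibited drug use.
- **The patients stay in the FAS.** This is true: they are imputed, not deleted. A reader might infer that the FAS drifts toward a per-protocol result. The documents do not support that. A per-protocol analysis leaves these patients out, whereas here early removals enter as zero change, and equal removal dilutes the effect.
- **Power.** A reader might infer that keeping follow-up would recover the 20% allowance and raise power by a stated amount. That is not supported either. The allowance covers all dropout and withdrawal, no share is attributed to these grounds, and a baseline with those patients deleted is not the planned FAS.
- **Scope of the grounds.** A reader might infer that stopping study drug by itself ends participation, or that investigators may remove patients for lack of effect. The voluntary-withdrawal section speaks of those who stop both medication and testing, or who cannot be reached. Ineffectiveness and intolerance appear there as reasons to record, not as investigator grounds.
- **Carry-forward causes the shift.** The quantified shift does come from the imputation. But the removal rule supplies the missing values on which the imputation acts, and observed outcomes would make it unnecessary.
- **Condensed article.** A fuller protocol might provide for assessment after removal, and the schedule figures are not shown. However, the article is not silent: it describes removal from the study followed by carry-forward, and that text is what needs changing.

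**Conclusion.** The concern holds as a design weakness of uncertain size. As written, the plan lets investigators end follow-up for three post-randomization reasons that can depend on treatment, and replaces the missing week-24 outcome with an earlier value. That conflicts with the purpose of the intention-to-treat analysis and serves no analysis that the PPS does not already provide.

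The figure of 0.17 to 0.21 MDNS points (25–30% of the planned difference) is an illustration, not an estimate. It assumes a 5-percentage-point imbalance in removal, all before week 12, baseline carried forward, and removed patients who would otherwise have had their arm's mean change. Later removals, or equal removal in both arms, would have different effects. The change is worth making because it is cheap and removes an avoidable source of bias, not because a particular loss has been shown.

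**What to change.** In Researcher's decision, separate being off study drug from being off study. State that poor compliance, prohibited drug use and unblinding do not end follow-up. Collect week-12 and week-24 MDNS and week-24 NCV for all randomized patients unless they withdraw consent to follow-up. Analyse these observed values in the FAS, and leave the PPS exclusions as they are. Align the carry-forward sentence in Subjects' voluntary withdrawal so that it no longer stands in for an assessment that could have been made. Whether study drug is stopped in any of these cases is a clinical rule left to the sponsor.

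The cost is a protocol amendment, communication to the six centers, and keeping some visits that are already scheduled. The FAS estimate may be slightly diluted by patients who are off drug. According to Trial status, 73 patients had been recruited at submission and none had completed treatment, so an amendment made then could still have protected the week-24 data.

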### Subjects’ voluntary withdrawal

As stipulated in their informed consent forms, the subjects have the right to withdraw from the study at any time. Participants who do not formally withdraw from the study but cease to accept medication and undergo testing or who become impossible to contact are also considered withdrawn. The researcher should realize and record the reasons for subjects’ withdrawal to the greatest extent possible, noting whether the treatment is obviously ineffective, difficult to tolerate owing to adverse reactions, or whether the patient cannot continue to participate in clinical research for some other reason, such as economic or personal factors. Whatever the reason, the case record should be retained; the last test results will be carried forward to the final result; and a full dataset will be analyzed for the treatment’s efficacy and adverse effects.

### Intervention measures

All patients in the group will be treated with conventional treatment, which includes oral mecobalamin (500-mg tablet three times per day), diet, exercise, and oral medicine, to ensure access to steady levels of blood glucose, blood lipids, and blood pressure according to American Diabetes Association guidelines. On this basis, subjects will be randomly assigned to receive placebo (6 g/bag two times per day) or TangBi Formula (6 g/bag two times per day) by the central randomization system using a randomly permuted block design with block sizes of two and four. Upon production, study medications will be packaged and transferred to numbered bottles by designated pharmacists according to the randomized list prepared by the trial statistician. The treatment will last for 6 months. All of the people involved in the trial (patients, investigators, project manager, data management team, clinical research associates, and statisticians) will be masked with respect to the group assignments. Outcome analyses will be performed by analysts blinded to the group assignments by use of a central randomization system in which the codes will be kept by an independent allocator and revealed only after treatment and analyses are completed.

